#### Family Caregivers

The eligibility criteria for adult family caregivers are that they are willing and able to deliver fundamental care during hospitalization (for a minimum of 8 hours per day) and after discharge (if needed). Furthermore, they should be nominated as the appointed family caregiver by the patient and should not require support from health care professionals to carry out their own self-care activities. Furthermore, family caregivers will have to be able to read and write the Dutch language and will be included after providing written consent. In this study, family caregivers could be relatives or close friends who know the patient and either live with or are involved in the care of the patient. They are individuals who provide support and with whom the patients have a significant relationship.

### Intervention

#### Overview

The FIP is a multicomponent intervention developed using a multiphase quality improvement design [26]. The main components of the program are as follows: (1) active involvement of family caregivers and (2) training and coaching of health care professionals in the FCC. The development process and rationale of this program have been described in further detail by Eskes et al [26]. The FIP is performed in addition to the usual postoperative care.

#### Component 1: Active Involvement of Family Caregivers

For the first component, multiple tasks involving families in fundamental care activities are described.

##### Invite Family Caregivers to Participate in Fundamental Care Activities

To standardize FIP delivery, family caregivers will be asked to participate in evidence-based fundamental care activities (Textbox 1). In addition, family caregivers can participate in optional care activities (Textbox 2).

Fundamental care activities executed by family caregivers.Three times a dayMobilization defined as getting a patient out of bed (ie, sitting out of bed and ambulation) [12,31-33]Encouraging oral intake and companionship during meals (ie, breakfast, lunch, and dinner) and ensuring that patients are seated at the table when meals are served [11,32]Supporting patients in doing breathing exercises (ie, coughing and deep breathing) [12,34,35]Supporting active orientation; specific time-, place-, and person-related information in the context of the present day; and daily discussions on actual items (eg, news) [31,32]Two times a daySupporting in carrying out oral care (brushing teeth and using mouthwash) [12,34,35]

Optional care activities executed by family caregivers.General careWashing and dressing of the patientAssistance with the use of the toiletWound-related careWound dressingAdministering medicationInjecting anticoagulationDrain-related careTaking care of abdominal drainsTaking care of nasogastric tubes

##### Information About Fundamental Care Activities

Family caregivers who participate in the FIP will gain access to a mobile app (so-called “Mantelzorgapp”) before patients’ hospital admission. The app has detailed descriptions of the following: (1) the rationale for performing the fundamental care activity, (2) preparation for the activity, (3) the needed material for the activity, (4) a step-by-step description on how to perform the activity, and (5) time and frequency of performing the activity. The app also includes a daily diary in which the family caregivers tick boxes if they have performed a fundamental care activity (yes or no) with writing space for comments. Furthermore, the app includes discharge information, such as whom to contact if they have concerns about patients’ health condition. The app can be downloaded without any cost from the Apple Store (Apple Inc) and Google Play Store (Google LLC) and is suitable for several mobile devices (ie, phones and tablets). If family caregivers are unable to use the app, they will receive paper-based information.

##### Shared Goal Setting With the Patient, Family Caregiver, and Nurse

On the basis of mutual agreement among the patient, the family caregiver, and the nurse, a personalized plan for the patient and family caregiver will be made within 24 hours after the surgery. This plan includes the patient’s care needs and personal goals of the family caregiver. This plan will be documented in the electronic patient record. Active participation will start on the first day after surgery in the ward (or within 72 hours in case of ICU admission) and will be continued for at least 5 days after surgery. After this period, the family caregivers choose whether or not to continue the program. We plan to work with the same family caregiver throughout the study period. However, if there are multiple family caregivers, we will recruit a maximum of 3 family caregivers who are available and interested. These family caregivers need to alternate during admission, and each family caregiver needs to be involved in the FIP for a minimum of one day.

##### Task-Oriented Training of Family Caregivers to Deliver Fundamental Care Activities

During the FIP, the family caregiver will receive training from a registered nurse. All the activities will be supervised by the nurse until the family caregiver is competent, as determined by the nurse, to carry out the activities on their own. To facilitate adequate care delivery, the objective of each activity, including instructions on how to deliver the activity, is described in full detail and accessible in the app. If the activity is carried out, the family caregiver registers it on the registration form in the app. Additional activities will also be recorded in the app.

##### Physical Proximity (Rooming-in)

Family caregivers are asked to stay with the patient for at least 8 hours per day during the first 5 postoperative days, which offers the opportunity to learn and become competent in new fundamental care activities under supervision. As most of these activities should be undertaken 3 times a day, presence of at least 8 hours provides them with the opportunity to complete these activities.

##### Presence of Family Caregivers During Medical Ward Rounds

Family caregivers are encouraged to be present and to be actively involved during medical rounds. Health care professionals (eg, doctors and nurses) will support the family caregivers throughout the hospital stay, answer questions related to the FIP, and identify unmet needs.

#### Component 2: Training and Coaching of Health Care Professionals

To support the delivery of the FIP, structured training sessions will be given to doctors and nurses. The training will mainly focus on the four core concepts of FCC: (1) dignity and respect, (2) information sharing, (3) participation, and (4) collaboration [26]. In the session, the rationale, goals, and benefits of the FIP and the concept of passive and active family involvement will also be explained. In addition, quality- and safety-related topics will be discussed. The training session will be delivered by one of the members of the research team.

### Usual Postoperative Care

Patients in the usual care group will receive care based on the Enhanced Recovery After Surgery principles, which include early mobilization, early postoperative feeding, goal-directed fluid therapy, and nonnarcotic analgesia [36]. In addition, patient engagement and a multidisciplinary team approach to the usual postoperative care will be used [36]. Patients will receive care pathways for their specific type of surgery in which day-to-day targets are provided, which promotes autonomy and cooperation from the patients. Patients are encouraged to actively mobilize from the day of surgery until hospital discharge (ie, stay out of bed for 2 hours on the day of surgery and at least 6 hours per day from the first postoperative day until hospital discharge). The patients will not receive detailed information about the content of the FIP. No rooming-in opportunities will be offered to the usual care group, except for family visits (ie, a maximum of 2 visitors at the patient’s bedside between 11 AM and 8 PM will be permitted).

### Outcomes

The primary patient outcome is the number of unplanned readmissions up to 30 days after surgery (Table 1). Secondary outcomes include the total number of complications at 30 and 90 days after surgery and the number of complications sensitive to fundamental care activities (eg, pneumonia, urinary tract infection, wound infection, deep vein thrombosis, malnutrition, and delirium) at 30 and 90 days after surgery. These data will be collected from patient records, and complications will be classified according to the revised version of the Clavien-Dindo classification system [37]. Secondary outcomes also include emergency department visits, ICU admissions up to 30 and 90 days after surgery, and hospital length of stay. Furthermore, patients’ QoL will be measured using the EQ-5D-5L [38], and the level of anxiety and depression in patients will be measured using the Hospital Anxiety and Depression Scale (HADS; Table 1) [39,40]. Patient satisfaction with care and sleep quality will be measured using the numeric rating scale (NRS) ranging from 0 to 10, with higher scores indicating higher satisfaction or sleep quality (Table 1). Sleep quality will be assessed once a day, from the first day after surgery until 5 days after the operation. In addition, the amount of home care (in hours per week) after discharge will be measured (Table 1). The risk screening scores routinely measured during hospital admission will be collected, ie, the Short Nutritional Assessment Questionnaire score (SNAQ) [41], the Delirium Observation Scale score (DOS) [42], the Braden scale [43], the Amsterdam UMC Extension of the John Hopkins Highest Level of Mobility scale score (AMEXO) [44] and the John Hopkins Fall Risk Assessment (JHFRAT; Table 1) [45].

In addition to the effect of the FIP on patient outcomes, we measured the effect of the FIP on family caregiver outcomes, including caregiver burden and well-being up to 90 days after participating in the FIP (Table 1). The Valuation of Informal Care Questionnaire (iVICQ) measures objective burden using the following items: duration and intensity of informal care, patient health, need for permanent surveillance, patients’ living situations, and use of professional care [46]. Subjective burden will be measured using the Caregiver Strain Index plus (CSI+) [47], self-rated burden scale [48], and perseverance time [49]. The well-being of family caregivers will be measured using the Care-related Quality of Life instrument (CarerQoL-7D) and Care-related Quality of Life–Visual Analog Scale (CarerQoL-VAS; Table 1) [50]. Finally, the costs of the FIP will also be measured using the iVICQ [46].

To measure adherence, which is considered a bottom-line measurement of intervention fidelity [51], we will record how many patients are offered the FIP and how many patients decline, including the reasons if they want to disclose. We will use the data recorded by family caregivers to assess the fidelity of the intervention. Up to 5 days after surgery, family caregivers will be asked to record the fundamental and optional care activities they have carried out in the app, and if not completed, to add a reason. The family caregiver registers the activity on the registration form of the app. If multiple family caregivers participate in the FIP, they will all be asked to record the executed activities. Rooming-in of the family caregivers during admission will be checked by ward nurses and researchers (SM, SK, and [name]).

**Table 1 table1:** Outcome variables for patients and their family caregivers.

					T0, baseline		T1, during 5 days after the operation			T2, at discharge		T3, discharge+30 days		T4, discharge+90 days

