**Patient**														
		Unplanned readmissions^a^										✓		✓
		Complications (sensitive to fundamental care activities)^a,b,c^										✓		✓
		First aid visit^a^										✓		✓
		ICU^d^ admission^a^										✓		✓
		EQ-5D-5L			✓				✓			✓		✓
		HADS^e^			✓				✓			✓		✓
		NRS^f^ patient satisfaction							✓					
		NRS sleep quality					✓							
		LOS^g^							✓					
		Bodyweight (in kilogram)			✓				✓			✓		✓
		Professional home care (indications)							✓			✓		✓
		SNAQ^h^			✓							✓		✓
		Braden scale			✓							✓		✓
		DOS^i^			✓		✓					✓		✓
		AMEXO^j^					✓					✓		✓
		JHFRAT^k^			✓							✓		✓

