**Family caregiver**														
	**Objective burden**													
			Duration of informal care	✓				✓			✓		✓	
			Intensity of informal care	✓				✓			✓		✓	
			Health of patient	✓				✓			✓		✓	
			Need for permanent surveillance	✓				✓			✓		✓	
			Patients’ living situation	✓				✓			✓		✓	
			Use of professional care	✓				✓			✓		✓	

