### Allocation

Participation in the FIP is based on the preferences of patients and, if available, their family caregivers. This means that when the patients and their relatives want to participate in the program, they will be allocated to the intervention group and when the patients or their relatives do not want to participate in the program (but give consent for observation in the usual care group), they will be allocated to the usual care group. By using this patient preference study design, we might introduce contamination between the intervention and comparison groups, as patients in the comparison group might learn about fundamental care activities and adopt them themselves or receive informal care without the program. Nevertheless, this study design was selected deliberately because no clear signs of contamination were observed between the study groups in the pilot study [16]. To minimize the risk of between-group contamination, the information for patients and their families before inclusion will not include detailed information about the fundamental care activities that comprise the program.

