### Data Collection Methods

#### Patients

At baseline, the following patient characteristics will be collected from the patient records: sex [53], age [53], length in cm, weight at admission in kg [54], BMI in kg/m^2^ [54], WHO performance status [55], American Society of Anesthesiologists Physical Status Classification (ASA PS Classification) [55], use of ≥5 medicaments [56], preoperative diagnosis, tumor type, type of surgery (ie, open, minimally invasive, or robot-assisted), and type of resection. In addition, the risk screening scores (ie, SNAQ, DOS scale, Braden scale, AMEXO, and JHFRAT) will be collected on the day of hospital admission. The number of days spent in the postanesthesia care unit will be collected from the patient records.

Furthermore, socioeconomic data will be collected via a patient questionnaire on the day of admission, including the highest level of formal education, marital status, number of children (≤18 years), and number of live-in children, hours per week of unpaid work and paid work [53]. The degree of social isolation before admission could be a potential confounder, as it is known that socially isolated patients have worse outcomes [57] and will therefore be measured using the Friendship scale [58].

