#### Outcomes

Univariable regression and multivariable regression analyses will be conducted using stepwise backward selection. For the primary outcome (ie, unplanned readmissions up to 30 days after surgery), we will conduct logistic regression analyses. For continuous secondary outcomes, we will use linear regression analyses; for dichotomous outcomes, we will use logistic regression analysis. We will use a general linear mixed model to analyze differences in sleep quality, DOS scores, and AMEXO scores over 5 days after the operation (Table 1). If a difference is observed, a post hoc power analysis will be used to examine which time point differs significantly. A 2-sided *P* value ≤.05 will be considered statistically significant. A 95% CI for the beta coefficient (β) will be calculated.

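### Table 1 omits the admission AMEXO that the text promises, and sleep quality and patient home care have no direct pre-surgery value, so adjustment of these secondary outcomes for self-selection is only partial

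*Protocol article*

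**What the plan says.** **Mobility (AMEXO).** The Patients subsection of Data Collection Methods states: "In addition, the risk screening scores (ie, SNAQ, DOS scale, Braden scale, AMEXO, and JHFRAT) will be collected on the day of hospital admission". In Table 1 the AMEXO row is ticked at T1, T3 and T4, with nothing at T0. The other four scores in that sentence all have a T0 tick.

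**Sleep quality.** The Outcomes section of the Methods says: "Sleep quality will be assessed once a day, from the first day after surgery until 5 days after the operation". Table 1 agrees, with a tick at T1 only.

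**Home care.** The same section says "the amount of home care (in hours per week) after discharge will be measured". The patient row in Table 1 is labelled "Professional home care (indications") and is ticked at T2, T3 and T4. Among the caregiver items, the row "Use of professional care" is ticked at T0 as well as at the later visits.

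**Analysis.** Under Statistical Methods, Outcomes: "We will use a general linear mixed model to analyze differences in sleep quality, DOS scores, and AMEXO scores over 5 days". No baseline value of the outcome is named as a covariate. The Statistical Methods overview makes confounder adjustment depend on baseline differences between the arms, which are tested for significance. The regressions use stepwise backward selection.

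**Allocation.** "Participation in the FIP is based on the preferences of patients and, if available, their family caregivers".

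**The concern.** This is a preference cohort, so nothing balances the arms before surgery. Entry to the programme needs a caregiver who can be present eight hours a day. The Discussion expects about 20% of patients to be unable to take part for want of a caregiver, and a further 15% of caregivers to decline. Having such a caregiver could plausibly be related to prior mobility, sleep and existing home care. The Discussion itself stresses comparing as many prognostic variables as possible.

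The outcome's own pre-surgery value is usually the strongest single covariate for that purpose. Where it is missing, a difference that predates surgery can be read as a programme effect. AMEXO matters in particular because mobilisation three times a day is one of the programme's core activities.

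The two home-care descriptions raise a separate difficulty. An indication for care and a number of weekly hours are different quantities and may call for different regression models.

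**Working it through.** The plan gives no figure on this point to reproduce. The main check sets the text beside Table 1.

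| Measure | Text | Table 1 | Pre-surgery value |
|---|---|---|---|
| SNAQ, Braden, JHFRAT | day of admission | T0, T3, T4 | yes |
| DOS | day of admission | T0, T1, T3, T4 | yes |
| AMEXO | day of admission | T1, T3, T4 | yes by text, no by table |
| Sleep NRS | postoperative days 1 to 5 | T1 | none direct |
| Patient home care | hours per week after discharge | T2, T3, T4, as indications | none direct |
| Caregiver-reported professional care (iVICQ) | at admission | T0, T2, T3, T4 | proxy for home care |
| EQ-5D-5L, HADS | patient questionnaires | T0, T2, T3, T4 | yes |

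Three things follow.

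1. AMEXO is a contradiction between text and table. The DOS row directly above shows T0 and T1 in separate columns, so a broken table is an unlikely explanation.
2. Of the three outcomes in the day 1 to 5 mixed model, only DOS has a baseline in both places.
3. Sleep and patient home care have no direct baseline in either place. The admission questionnaire, as described, covers education, family, work and social isolation.

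**Illustration of size.** The inputs are 150 per group (Sample Size section), an assumed baseline imbalance d = 0.3 SD and an assumed baseline-to-outcome correlation r = 0.4 to 0.6. The comparison is at a single time point with outcome SD 1, no true effect and no adjustment.

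- Standard error of the difference: √(2/150) = 0.115 SD.
- Bias: r × d = 0.4 × 0.3 = 0.12 SD, to 0.6 × 0.3 = 0.18 SD.
- In standard errors: 0.12/0.115 = 1.0, to 0.18/0.115 = 1.6.
- Two-sided false-positive rate, Φ(bias/SE − 1.96) + Φ(−bias/SE − 1.96): about 18% to 34% instead of 5%.
- Wider assumptions (d = 0.2 to 0.5, r = 0.3 to 0.7): bias 0.06 to 0.35 SD and a false-positive rate of 8% to 86%. The result is driven by the assumptions.
- Residual variance removed by a baseline covariate: r² = 0.16 to 0.36.

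**Why adjustment should not depend on a baseline test.** An imbalance of 0.3 SD lies 0.3/0.115 = 2.6 standard errors from zero. A 5% test detects it with probability of about Φ(2.6 − 1.96) = Φ(0.64) = 0.74. An imbalance of that size would therefore go unflagged about one time in four, and backward selection could still drop the covariate afterwards.

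**The case against.** A reader might infer that pre-surgery differences cannot be removed from any of the three outcomes, or that nothing relevant is ever recorded. The documents do not support that.

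- **AMEXO.** If the Data Collection section is followed, an admission score exists and can be adjusted for. What remains is a conflict to reconcile, plus the absence of a fixed role for that score in the model.
- **Home care.** The caregiver-reported item at T0 is a usable proxy. It is imperfect, because it does not come from the patient, its unit is not given, and it may be absent for usual-care patients who have no caregiver.
- **Sleep.** The outcome describes sleep during recovery in hospital, and a recalled rating of earlier sleep would be a different quantity. T0 HADS and EQ-5D-5L, performance status, ASA class and the Friendship scale allow partial adjustment. Only the part they do not explain stays uncorrected.

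Two further objections have weight. The article is condensed and introduces the questionnaire's content as an inclusive list, so items on usual sleep or current home care may exist without being shown. The bias figures rest on no number in the documents and describe one unadjusted comparison, whereas the plan has a repeated-measures model and multivariable adjustment.

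The text-table conflict on AMEXO, the two definitions of home care and the explicit postoperative start of sleep measurement still stand. So does the data-dependent route by which covariates enter.

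**Conclusion.** The point holds in a limited form. Table 1 and the text must be reconciled on admission AMEXO, and home care has two incompatible descriptions. Sleep and patient home care have no direct pre-surgery value in the document, so adjustment for self-selection on these outcomes is partial. It is neither absent nor complete.

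Only secondary outcomes are touched, and unplanned readmission is unaffected. The size of any bias cannot be derived from the documents. The 0.12 to 0.18 SD figure depends on the assumed imbalance and correlation and applies before any adjustment through other covariates. It would not apply to AMEXO if the admission score was collected and is used.

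**What to change.** 1. **Reconcile AMEXO.** Establish whether admission scores were recorded, then correct Table 1 or the Data Collection text.
2. **Fix the covariates.** Where the admission values exist, enter admission AMEXO in the AMEXO model and admission DOS in the DOS model over days 1 to 5, whatever the baseline tests or backward selection show.
3. **Define home care once**, as hours per week, in both text and table. Adjust it for the caregiver-reported T0 item where available, and report how often that item is missing in each arm.
4. **Adjust sleep for T0 HADS and EQ-5D-5L.** First confirm that these were completed before surgery: the text places the patient questionnaire on the day of admission, while Table 2 lists questionnaires on baseline characteristics within 24 hours after surgery.
5. **State the limitation.** Report that sleep and home care lack a direct baseline. If the full questionnaire does hold such items, use them instead.

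The cost is a table correction, a few sentences in the analysis plan and one limitation statement. All the covariates named are ones the protocol says it collects. The last participant's follow-up ended in May 2022, so new T0 questions on sleep and home care could serve only a future cohort, at the price of two extra questionnaire items.
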